#### ATSA

ATSA tracks call attempts, call outcomes (completed vs. incomplete), and reported symptom scores. The number of completed calls relative to call attempts will be used to describe patient uptake of the intervention as well as the dose received.

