### Monitoring and Reporting of Adverse Events

The study includes several mechanisms for monitoring and identifying adverse events. First, symptom data from ATSA are reviewed weekly by the Principal Investigator (PI) who is a physician. When a patient reports multiple symptoms at severe levels (7 or above), the PI reviews the medical record to insure that the symptoms have been recognized by oncology staff. In the event that there are no progress notes indicating that the patient has been recently seen or contacted, the PI calls the oncology nurse case manager to alert them to the patient's reports.

When patients fail to respond to ATSA calls on two consecutive days, research staff calls the patient to ensure their safety. When patients cannot be reached, study staff informs the caregiver and oncology nurse case manager. Patients who are hospitalized are given the option to suspend their ATSA calls. Patients enrolling in hospice are given the option to come off study.

Subjects and clinicians have access to a toll-free number they can call with study-related problems. Caregivers have access to the research team's contact information through the website. Adverse clinical events are reported immediately to the clinician of record as well as the IRB. All deaths are immediately investigated by a physician not affiliated with the study in order to determine the cause.

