#### Primary Analytic Strategy

The primary effect of the intervention will be determined using data obtained at 10 weeks, and the sustained effect will be determined using data obtained at 14 weeks. Cross group comparisons will be made based on an intention-to-treat basis. We will also test the hypotheses with a longitudinal design by fitting a linear mixed-effects modelor a generalized linear mixed effects model to estimate effect averaged over 10 and 14 weeks, adjusting for potential within-person correlation and baseline values of the outcome variables [15].

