#### Missing Data

When missing values occur, we will determine whether missingness is random or associated with patient or caregiver characteristics using standard regression models. As long as we do not observe any bias in patterns of dropout or missing data (see attrition analysis above), we will use regression techniques allowing for missing at random. Models will include 10 and 14 week assessment data as longitudinal outcome values, an intervention effect indicator, and baseline values of the outcome variable and other covariates as fixed independent variables. If the analyses indicate that missingness depends on unobserved outcome values(, we will account for missing data using a pattern mixture model [43]. This technique allows the use of data from all participants (not just completers) and provides an unbiased intervention effect estimate.

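### The missing-data rule turns on a condition the data cannot show, calls the pattern-mixture estimate unbiased without qualification, and states a model that does not isolate the week-10 primary effect

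*Protocol article*

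**What the plan says.** The Missing Data section works in three steps.

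- **Diagnosis:** "we will determine whether missingness is random or associated with patient or caregiver characteristics using standard regression models".
- **Default:** "As long as we do not observe any bias in patterns of dropout or missing data", with a pointer back to the attrition analysis, regression that allows for missing at random is used. The model described has the week-10 and week-14 assessments as longitudinal outcomes, one indicator for the intervention, and the baseline outcome and other covariates as fixed terms.
- **Switch:** "If the analyses indicate that missingness depends on unobserved outcome values", then "we will account for missing data using a pattern mixture model". The section says this technique uses everyone's data and "provides an unbiased intervention effect estimate".

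Primary Analytic Strategy places the primary effect at week 10 and the sustained effect at week 14, with comparisons by intention to treat. It adds a longitudinal mixed model "to estimate effect averaged over 10 and 14 weeks". Hypothesis Testing gives the week-10 analysis as a regression of the summed symptom score on study group and baseline score. Attrition Analyses compares baseline characteristics of dropouts and reasons for attrition by group, and answers any difference with covariate adjustment or stratification on a propensity score in the primary analysis. Sample Size Calculation allows for 25% attrition and targets a difference of 0.33 SD.

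**The concern.** A rule for choosing the missing-data method should be one that an analyst can apply. This one asks whether missingness depends on outcomes that were not seen. The stated tools (regressions on characteristics, comparison of dropouts, reasons for leaving) use only observed data. They can show that data are not missing completely at random. They cannot separate missing at random from missing not at random. In practice the method would be chosen by judgement after seeing the data.

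The claim of unbiasedness then gives the reader an assurance that the method cannot provide. Finally, the model written for incomplete data appears to answer a different question from the declared primary one. With a quarter of patients expected to be lost, how missing scores are handled matters for the primary result.

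**Working it through.** **Inputs from the protocol.** 25% attrition, 112 analysable dyads per arm, 300 enrolled, target 0.33 SD (Sample Size Calculation). The attrition step reproduces: 112 / 0.75 = 149.3, so 150 per arm and 300 in total. Every other input below is an assumption.

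**1. The trigger.** Suppose dropout depends on the week-10 score in the intervention arm only (logit intercept -1.3, slope 1.0), the coefficient on baseline is 0.5, and the true week-10 effect is -0.33 SD. With 200,000 simulated patients, about 20% were missing in the intervention arm and 21% in control, yet the baseline-adjusted week-10 estimate was about -0.465. Similar dropout rates gave no warning. A regression of missingness on characteristics could find a link with baseline here, but not the dependence on week 10 that remains after baseline is accounted for.

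**2. The unbiasedness claim.** Let the unobserved scores of dropouts differ from their missing-at-random prediction by δ_I in the intervention arm and δ_C in control. With a fraction m missing in each arm, the effect moves by m × (δ_I - δ_C). With m = 0.25:

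| δ_I - δ_C (SD) | Change in effect (SD) |
|---|---|
| 0 | 0 |
| 0.20 | 0.05 |
| 0.25 | 0.0625 |
| 0.33 | 0.0825 |
| 0.50 | 0.125 |

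The observed data do not fix δ_I or δ_C. The analyst supplies them, so the estimate is unbiased only if that choice is right. The largest value shown is 0.125 / 0.33 = 38% of the target difference.

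**3. The quantity estimated.** With one intervention indicator and both visits observed, the model targets (d10 + d14) / 2. With d10 = 0.33 SD:

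| d14 (SD) | Averaged effect (SD) |
|---|---|
| 0.33 | 0.33 |
| 0.20 | 0.265 |
| 0.165 | 0.2475 |
| 0.10 | 0.215 |
| 0 | 0.165 |

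The average equals the week-10 effect only when the effect is the same at both visits. In simulation with ignorable dropout, d10 = -0.33 and d14 = 0, the single-indicator model gave -0.17, against the formula's -0.165.

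**4. How much bias dropout might cause in the week-10 regression.** Assumptions: no true effect; a mid-study score correlated 0.6 with baseline and 0.7 with week 10; week 10 and week 14 correlated 0.7; dropout logit with intercept -1.35 and a slope on the mid-study score; about 23% dropout.

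| Slopes, control / intervention | Analysis | Bias (SD) |
|---|---|---|
| 1.0 / 0.4 | Week-10 regression in those observed | 0.059 |
| 1.0 / 0.4 | Week-10 contrast from a 10/14-week model, dropouts miss both surveys | 0.062 |
| 1.0 / 0.4 | Same model, 30% of dropouts return at week 14 | 0.052 |
| 1.0 / 0.4 | Imputation by arm using the mid-study score | 0.001 |
| 0.8 / 0.6 | Week-10 regression in those observed | 0.017 |
| Equal | Week-10 regression in those observed | about 0 |

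In the first scenario sicker controls leave, so the bias runs against the intervention; with the slopes exchanged it would favour it. The longitudinal model does not help because a patient with no follow-up survey contributes nothing to it beyond baseline.

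**The case against.** Several points on the other side are fair.

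- **Observed differences in attrition.** A reader might infer that any link between dropout and characteristics makes the plan abandon missing-at-random methods. The documents do not support that. Attrition Analyses responds with covariate or propensity adjustment, which is conditioning on observed variables, and the pattern-mixture step has its own trigger.
- **The primary estimand.** A reader might infer that the primary analysis has become an average, or is confined to completers. The averaging is worded for an additional analysis, the week-10 regression stays in the plan, and no text limits it to patients with a week-10 survey. What stands is that the only model described for incomplete data has one indicator over both visits, and that nothing links it to the week-10 regression.
- **Unused weekly scores.** The automated system stores them ("ATSA tracks call attempts, call outcomes (completed vs. incomplete), and reported symptom scores"), but leaving them out of a condensed article is not an error, and the model admits other covariates. Using them is an improvement.
- **Hospice.** The protocol says "Patients enrolling in hospice are given the option to come off study". It is tempting to read this as loss of the surveys among the sickest patients. The text gives an option and does not say that surveys stop, so no finding rests on it.
- **The trigger as judgement.** Reasons for attrition can inform how plausible informative dropout is, and a stray bracket suggests that words are lost from the trigger sentence. No lost words could make unobserved values observable, and a judgement is better expressed as a sensitivity analysis that is always run.

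**Conclusion.** The point holds in three parts that need no simulation: the trigger cannot be evaluated, the unbiasedness claim is wrong without its condition, and the stated missing-data model targets the week-10 effect only if the effect is constant from week 10 to week 14. There is also a gap: the plan does not say how missing scores enter the week-10 regression.

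The size of any bias is not known. The range of about 0.06, 0.02 and 0 SD (at most 0.059 / 0.33 = 18% of the target) depends wholly on assumed differences in dropout mechanism between arms, for which the protocol gives no figure. It should not be read as a forecast. Likewise 0.215 SD follows from an assumed week-14 effect of 0.10 SD.

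**What to change.** 1. Delete the trigger sentence and the word unbiased from Missing Data.
2. Prespecify one primary analysis in all randomised patients that gives the week-10 contrast under missing at random, whatever the attrition comparison shows. Preferably use multiple imputation by arm from baseline and the stored weekly automated symptom scores, followed by the regression in Hypothesis Testing. The automated ratings and the interview are different modes, so the weekly scores serve only as auxiliary variables.
3. If a longitudinal model is kept, include arm-by-visit and baseline-by-visit terms and read the week-10 contrast. Without the weekly scores this corrects the quantity estimated, but does not remove bias from dropout that follows mid-study worsening.
4. Always run a delta-adjusted pattern-mixture analysis over a stated range as a sensitivity analysis, and report deaths by arm separately from other missing data.

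The cost is a little more analysis work on data already collected. No extra patients, visits or instruments are needed.

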#### Hypothesis Testing

We will compare summed symptom scores at 10 weeks between the control and intervention groups using a multiple regression model. The model will include a dummy variable for study group assignment as the main independent variable and will be adjusted for baseline symptom scores. While we do not expect the groups to be unbalanced with respect to other potential predictors of the outcome, we will adjust for these if randomization is not fully successful. The parameter estimate of the group assignment dummy variable and its statistical significance will estimate and test for the outcome difference between the two study groups at week 10, adjusting for baseline values of the outcome. A similar approach will be used to test the intervention effect on secondary outcomes (namely physical functioning, service utilization, and chemotherapy adherence). To determine if there is maintenance of the intervention effects on each outcome, we will use a similar regression model using the corresponding measurements at week 14, and a longitudinal model for the outcomes at 10 and 14 weeks.

Our analytic approach for testing Hypothesis 2 will be similar to that described above. We will use multiple regression models to compare group differences in patient-reported social support scores as measured by the Inventory of Socially Supportive Behaviors at 10 weeks, adjusting for baseline values of the ISSB [38]. The model will include a dummy variable for study group assignment as well as the baseline value of the ISSB scores, and the parameter estimate of the dummy variable will estimate the intervention effect on caregivers at 10 weeks. A similar approach will be used to test the intervention effect on caregiver burden and distress.

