*Hypothesis 2a: Caregivers receiving the intervention will provide significantly more social support to patients at 10 and 14 weeks as evidenced by increases in patient-reported measures of social support when compared with caregivers who do not receive the intervention*.

*Hypothesis 2b: Caregivers receiving the intervention will report lower perceived caregiving burden and distress compared to caregivers in the comparison group*.

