Decision making	**→**	Caregivers are asked to commit to trying three to five tasks for the week from the list of recommendations. To help caregivers make informed decisions about which recommendations to adopt, the Web site describes each task's purpose and what is involved, and provides examples for how to accomplish it.
		
Solution implementation & verification	**→**	After committing to 3-5 tasks, caregivers can print a list of their choices, or "Task List, " for future reference (Figure 1d). The next time the caregiver logs into the website, she is asked which of the tasks she attempted and whether the recommended action was helpful (Figure 1e). In addition to allowing caregivers to self-monitor the outcomes associated with their assistance, the data allow the investigative team to determine uptake of specific advice offered by Cancer CarePartners and caregivers' perceptions about its benefit.

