### Eligibility

Study patients must be 21 years or older, cognitively intact, English speaking, able to hear, and able to use the phone. They must have home access to a touch-tone telephone. They must have a solid tumor; for example, prostate, lung, colorectal, breast, non-Hodgkin lymphoma, or head/neck cancer. Patients may have new or recurrent disease in early or late stage. All patients must be within 10 weeks of initiating chemotherapy and, if they are being treated for recurrent disease, must have experienced a treatment free interval of 10 weeks between the new and past treatment. Patients may live alone or with others, with or without an in-home caregiver. Patients are excluded if they have been diagnosed with a hematologic malignancy or their treatment regimen involves bone marrow transplantation because such patients' symptom profiles differ from those of other cancer patients. Also, patients will be excluded if they (a) have untreated mental illness or cognitive impairment limiting their ability to participate with ATSA, (b) cannot identify at least one potential consenting caregiver, (c) are institutionalized or enrolled in hospice prior to enrollment, or (d) plan to discontinue receiving the majority of care from one of the study sites during the follow-up period.

For the purposes of this study, a potential caregiver *is defined as a person living inside or outside of the patient's household who has at least monthly contact with the patient, either by phone or in person, and is willing to help the patient manage his/her symptoms*. S/he must be 21 years or older, cognitively intact, English speaking, and able to hear and speak English for telephone interviews. S/he must have access to a telephone and computer with a high-speed Internet connection.

Caregivers need not be providing direct care prior to the study; indeed, a major motivation for this intervention is that many well-intentioned friends and family members would be willing to provide more cancer support, but currently do not do so because there is no structure in place to make that possible. Caregivers will be excluded if they, themselves, are on active treatment for cancer. They will also be excluded if they have poorly controlled mental illness, moderate cognitive impairment, or are unable to be interviewed by telephone.

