After completing the baseline assessment, participating patients are randomized to either the control or intervention arm by a computer minimization program that balances the arms for type of cancer (lung vs. other) and the type of caregiver (in-home vs. out of home). The minimization procedure, known as 'adaptive randomization' balances trial arms according to the history of previous allocations. Arms are being balanced for lung cancer since patients with lung cancer have a symptom pattern distinct from patients with other solid tumors [34,35]. Arms are being balanced for type of caregiver because in-home caregivers have more access to the patient than do caregivers living at a distance and, hence, more opportunities for providing support.

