## Discussion

Cancer patients undergoing chemotherapy experience many symptoms which they can manage when given the appropriate amount of information. However, self-management may not be sufficient or plausible for everyone. To provide added support to patients for-whom self-management is challenging, we designed Cancer CarePartners-a system offering automated telephonic monitoring of patients with alerts and customized advice to a caregiver via the Web. Our goal is to show that Cancer CarePartners can enhance caregiver support for the patient, so that patients engage in better self-management, and, in turn, experience better symptoms, function, and adherence with chemotherapy, ultimately requiring fewer formal resources during and after treatment. If successful, this intervention will be among the first to demonstrate that caregivers can be formally engaged to improve clinical outcomes.

While we hypothesize that Cancer CarePartners will also reduce caregiver burden and distress by enhancing caregiver knowledge and mastery, it is possible that the opposite may occur; thus, we will closely monitor caregiver outcomes throughout the study. Should caregivers experience increased burden from the intervention, the reasons will need to be explored qualitatively in order to inform the redesign of the system or revise caregiver materials so that they are fully informed of the risks prior to using Cancer CarePartners.

One potential limitation of the study is that not all patients will have access to a caregiver with access to the Web. Additionally, some patients, regardless of their access to a caregiver, may not want to involve others in their care or may prefer a 'human touch' over automation. We will closely monitor reasons for exclusion, refusal and drop out to understand the prevalence of these concerns so as to determine the generalizability of our results. Still, we do not expect that Cancer CarePartners will be appropriate for everyone. We posit that some patients will continue to want or need the support of clinicians by phone or face-to-face. Cancer CarePartners is meant only to help clinicians more efficiently use their time, not replace them.

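### The caregiver burden and distress models leave out caregiver location, a minimization factor, and their single average effect cannot show harm confined to one kind of caregiver

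*Protocol article*

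**What the plan says.** All references are to the protocol article.

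- **Hypothesis 2b (Background):** "Caregivers receiving the intervention will report lower perceived caregiving burden and distress compared to caregivers in the comparison group". It is an arm-against-arm statement and names no subgroup.
- **Hypothesis Testing:** for patient-reported social support, "The model will include a dummy variable for study group assignment as well as the baseline value of the ISSB scores". The next step is "A similar approach will be used to test the intervention effect on caregiver burden and distress". Other predictors are added only if randomization proves not fully successful. Baseline Analysis likewise lists caregiver location among the characteristics to check, with adjustment or propensity stratification if a significant difference appears.
- **Eligibility:** patients may or may not have an in-home caregiver. A caregiver may live elsewhere and have contact as seldom as monthly, and "Caregivers need not be providing direct care prior to the study".
- **Table 1, decision making:** "Caregivers are asked to commit to trying three to five tasks for the week from the list of recommendations". Under Comparison group, control caregivers receive an emailed booklet.
- **Recruitment & Randomization:** "Arms are being balanced for type of caregiver because in-home caregivers have more access to the patient than do caregivers living at a distance".
- **Caregiver harm:** Background describes an earlier nurse-led telephone trial in which caregivers showed no change in distress overall while some had more depressive symptoms. The Discussion says of the hoped-for fall in burden and distress that "it is possible that the opposite may occur", and promises close monitoring of caregiver outcomes.

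**The concern.** The trial recruits people already giving care together with people who give no direct care, and asks those in the intervention arm to take on weekly tasks. It is plausible, though no passage says so, that advice lightens the load for the first kind and adds load for the second, who have little caregiving burden to lose. The stated analysis returns one arm effect averaged over both. A null or mildly favourable average could then be reported as reassurance while one kind of caregiver is worse off. The earlier trial cited in the Background shows why this matters here: an unchanged overall result sat beside worsening in some caregivers.

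There is also a smaller technical gap. Location is used to balance the arms but is not a fixed term in the caregiver models. Randomization keeps the average effect valid without it. But if location predicts burden or distress, leaving out a factor used in the minimization tends to give a standard error that is too large, and making its inclusion depend on observed imbalance leaves the model to be settled after the data are seen.

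**Working it through.** **Inputs from the article.** 112 completing dyads per arm, two-sided 0.05 (Sample Size Calculation). The enrolment goal reproduces: 224 / (1 - 0.25) = 299, rounded to 300. The calculation behind 112 was made for symptom severity and social support, not for burden or distress. A two-sided test at 0.33 SD with 80% power needs 145 per arm, and 112 gives about 69%. That is a separate matter; here 112 is used only as the number analysed.

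**Assumptions (the article gives none of these).** In-home share 50% or 70%; location-specific effects of -0.30, 0 or +0.30 SD (positive means more burden); baseline-outcome correlation r of 0 or 0.6, the same in both location groups.

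**Formulas.**

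- Average effect = share × in-home effect + (1 - share) × out-of-home effect.
- SE of an arm effect with n per arm = sqrt(1 - r²) × sqrt(2/n).
- SE of the interaction = square root of the sum of the two squared location-group SEs.
- Power by the two-sided normal approximation.

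**1. Opposite effects, half in-home.** Average = 0.5 × (-0.30) + 0.5 × 0.30 = 0, so the planned test rejects 5% of the time. With 56 per arm in each location group and r = 0.6, each SE = 0.8 × sqrt(2/56) = 0.151 and the interaction SE = 0.151 × sqrt(2) = 0.214. Then 0.60 / 0.214 = 2.81, power about 80%. With r = 0 the interaction SE is 0.267, the ratio 2.24 and power about 61%.

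**2. Opposite effects, 70% in-home.** Average = 0.7 × (-0.30) + 0.3 × 0.30 = -0.12 SD, which points to benefit while 30% of caregivers are worse by 0.30 SD. Out-of-home n is 33.6 per arm. A test within that group detects the 0.30 SD harm about 34% of the time (r = 0.6) or 23% (r = 0).

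**3. Location as an imperfect proxy.** If a quarter of each location group behaves like the other kind of caregiver, scenario 1 gives an in-home effect of 0.75 × (-0.30) + 0.25 × 0.30 = -0.15 and an out-of-home effect of +0.15. The contrast halves to 0.30 SD, and interaction power falls to about 29% (r = 0.6) or 20% (r = 0).

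**4. Harm with no offsetting benefit.** With effects of 0 in-home and +0.30 out-of-home, half each, the average is +0.15 SD. The average test and the interaction test then have the same power: about 29% (r = 0.6) or 20% (r = 0).

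**5. Precision of the location-specific estimates.** With half in-home, the 95% half-width is 1.96 × 0.151 = 0.30 SD (r = 0.6) or 1.96 × 0.189 = 0.37 SD (r = 0).

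**6. Multiplicity.** The CRA has five dimensions. With the CES-D, at two time points, that is up to 12 interaction tests. If they were independent with no true interaction, the chance of at least one false positive is 1 - 0.95^12 = 46%.

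**The case against.** The strongest reply is that nothing here is an error. Hypothesis 2b concerns an average, and a randomized comparison with a single arm term estimates that average whether or not effects vary. Subgroup lists are commonly left to an analysis plan, which is not shown. This stands. A reader might infer that the model assumes one common effect, or that the test is invalid; neither follows.

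Other stronger readings also fail:

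- **That effects do cancel.** Shares and effects are assumed throughout, and exact cancellation comes from choosing equal and opposite effects in equal halves. No passage predicts opposite effects by location.
- **That out-of-home means giving no care.** Eligibility does not equate the two. A housemate may give little help and an outside relative much. Potential caregivers are also approached in order of their involvement in the patient's life, which favours people already engaged.
- **That the Discussion will look for harm only in the average.** It ties its response to caregivers experiencing more burden, without saying how that is judged.
- **That the earlier trial's affected caregivers were newly engaged.** The Background does not say who they were.
- **That the room-to-fall argument covers both outcomes.** It concerns caregiving burden and does not carry over directly to the CES-D, a general depression scale.

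What the reply does not answer is that the article settles how location is handled, making adjustment depend on observed imbalance although location is a minimization factor. Adjusting for imbalance also says nothing about effects that differ. And the article foresees a harm that the one comparison it states cannot locate.

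**Conclusion.** The point holds in limited form. The planned comparison validly tests Hypothesis 2b, but it omits a minimization factor except under observed imbalance, and by construction it cannot separate harm in one kind of caregiver from relief or no change in another. The size is not knowable from the documents. In the assumed scenarios the average ranges from 0 to -0.12 SD while one group is worse by 0.30 SD. An interaction term would detect the difference with roughly 20% to 80% power, depending on the baseline correlation, the effects and how well location stands in for prior caregiving. A location-specific estimate therefore serves to show the range of effects compatible with the data, not to prove or exclude harm. The primary symptom analysis is unaffected.

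**What to change.** In Hypothesis Testing, for the CRA and CES-D models:

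1. Include caregiver location as a covariate whatever imbalance is observed.
2. Keep the average arm effect as the test of Hypothesis 2b.
3. Add a prespecified secondary group-by-location estimate, with the arm effect and 95% interval in each location group, presented as estimation of possible harm and not as further confirmatory tests.
4. State that location is only a proxy for caregiving before the study, and that a null or favourable average will not by itself be read as absence of harm in either group.

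**Cost.** Wording only: location is already recorded and balanced. The location-specific intervals will be wide and the interaction power limited, as shown above. Several extra estimates across the CRA dimensions and the CES-D will need cautious reading for multiplicity.
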